### Inpatient data collection: cluster randomisation with crossover

Patients will be admitted to one of the orthopaedic wards (clusters) through normal hospital procedures.

The wards will have been randomly assigned to a sequence of control (A) and intervention (B). The intervention, “B”, will be allocated to at least four cohorts. The intervention appears once in each period and twice in each of the two wards. Ward 1 will use the sequence ABBA and on Ward 2 the sequence BAAB and Ward 3 will be assigned AAAA (Fig. 1). Each cohort within a cluster (data collection period) will be accrued and monitored over a period for 12–15 weeks. To mitigate any risk of contamination between control and experimental groups, a wash out period (usual care on all wards, no intervention or data collection) between cohorts will be of approximately 2 weeks in duration.

Participants admitted to the control wards (A) during data collection periods will receive usual care based on the clinical pathways for TKR recovery. In addition to usual care, patient participants admitted to the intervention (B) ward during data collection will receive the multimedia intervention (via iPad™) each day, commencing on Day 1 after surgery.

#### Day 3 – data collection

Data will be collected from each participating patient in a cohort of a ward (A or B conditions) on postoperative Day 3. On this day, patients will be interviewed by the researchers and invited to respond to questions about their pain intensity, interference of pain on activities of daily living and to describe processes of care and interactions with clinicians relating to their goals of recovery. In addition, patients on the intervention ward (B) will also be invited to respond to questions related to the intervention. Table 2 outlines the concepts, measures and tools used during this data collection period.

**Table 2 Tab2:** Concepts measured and tools used for primary and secondary outcomes

Concept measured on day 3	Tool used
1. Pain intensity	• Numerical Rating Scale (NRS) [31]
2. Pain quality	• American pain society outcome questionnaire (APSOQ) (Cronbach α = 0.85) [32]
3. Pain treatment and management	• Medial record audit
4. Preference for participation	• Patient Activation Measure (PAM) • Control Preference Scale (CPS)

#### Medical record audit

Patients’ medical records will be audited on Day 3 to elicit analgesic administration over the 24 h period prior to the patient interview. The audit of pain treatment will involve review of medication charts to determine the type, dose and frequency of analgesic medications prescribed and the amount of analgesics administered as a ratio of administered verses available treatment in the 24 h period prior to interview.

### Follow up

A follow up questionnaire will be mailed to participants 4 weeks after they are discharged from the acute care ward. The concepts measured in this questionnaire include preference for participation (PAM & CPS), pain and functioning of knee after knee surgery (OKS), and patient satisfaction (NET promoter & global satisfaction) see Table 3. Patients will be asked to return the completed questionnaire using the pre-paid envelope provided. A reminder follow up telephone call approximately 2 weeks after the questionnaire mail-out will be made to remind patients to return the questionnaire.

**Table 3 Tab3:** Concepts measured and tools used for post discharge Questionnaire

Concept measured on day 3	Tool used
1. Preference for participation	• Patient Activation Measure (PAM) [28] • Control Preference Scale (CPS) [29]
2. Pain and functioning of knee after knee surgery	• Oxford Knee Score (OKS)
3. Patient Satisfaction	• NET promotor and global satisfaction

Data related to complications and readmission to hospital (within 28 days of discharge) will be obtained through hospital information systems and chart audits.

### Tools used for data collection

#### Patient activation measure

The Patient Activation Measure (PAM) [29] is a 22-item questionnaire that assesses patients’ knowledge, skill, and confidence for self-management [30]. The short form version [6] used in this study, has 13-items measured in four stages: 1) believes active role is important, 2) confidence and knowledge to take action, 3) taking action, and 4) staying the course under stress.

#### Control preference scale

The control preference scale (CPS) is a five item ordinal scale to measure preference for treatment decision making role. Control preferences are defined as “the degree of control an individual wants to assume when decisions are being made about medical treatment” [31]. The CPS consists of five questions that each portrays a different role in treatment decision-making using a statement. Patients will be asked to rank their participation preferences in order from most preferred option to least preferred option. This tool will be used both preoperatively and postoperatively to identify patients’ preference for participation in postoperative activities during their hospitalisation at the time of discharge.

#### American pain society patient outcome questionnaire-revised

This is a validated instrument that has been widely used internationally [32]. The questionnaire is designed for use in adult hospital pain management quality improvement activities and American Pain Society’s Patient Outcome Questionnaire (APSOQ-R) measures six aspects of quality: (1) pain severity and relief; (2) impact of pain on activity, sleep, and negative emotions; (3) side effects of treatment; (4) helpfulness of information about pain treatment; (5) ability to participate in pain treatment decisions; and (6) use of non-pharmacological strategies.

#### Numerical rating scale

The numerical rating scale (NRS) [33] is a 0–10 point scale where patients are asked to rate their pain using a whole number ranging from 0 (no pain) to 10 (worst pain).

#### NET promoter scale

This scale is used to determine patients’ satisfaction with hospital care. This single item question elicits patients’ willingness to recommend the health care facility to family or friends on a scale of 0–10.

#### Oxford knee score

The Oxford Knee Score (OKS) is a 12-item patient self-report questionnaire specifically designed and developed to assess function and pain after total knee replacement (TKR) surgery. It is short, reproducible, valid and sensitive to clinically important changes [34]. Use of the tool is widely reported in research literature and has been adapted and validated in several languages [35–37].

### Process evaluation

The process evaluation is designed to examine the delivery of the intervention and understand the effects (or not) in the context of acute care delivery [38]. In order to know if the multimedia intervention was successful or not, in reducing patient participant pain intensity scores on Day 3, underlying processes need to be examined.

Process evaluation in this trial will include patient participant semi structured interviews on Day 3 post operatively of all participants, to examine patient barriers and facilitators to participation in care. Specific questions will be asked of participants relating to their goals of recovery in order to describe processes of care and interactions with clinicians. In addition to the interviews, field notes will also be kept by the researches to record information about ward culture and organisational environment that may impact on patients’ ability to participate.

Medication chart and medical records audits will be conducted on Day 3 to elicit information regarding prescribing and administration of analgesia. Furthermore medical records will be audited for documentation regarding pain though out the 24 h period on Day 3, this will give us details of the management and recording of patient participants’ pain.

### Outcome measures

The effectiveness of the multimedia intervention will be assessed by the following outcome measures:The primary outcome is the difference in patients’ reported pain intensity (Numerical Rating Scale) on Day 3 between control and intervention group.Secondary outcome measures include:Interference of pain on activities of daily living (APSOQ-R) on Day 3Length of hospital stay (days)Function and pain following TKR surgery (Oxford Knee Score) 4 weeks after discharge from acute carePatient overall satisfaction (NET promotor score) 4 weeks after discharge from acute carePostoperative complications – Deep Vein Thrombosis (within 28 days)Readmissions to hospital (within 28 days)To conduct a detailed concurrent process evaluation to examine the delivery of the intervention and understand the effects of the intervention in activating patient participation in the context of acute care delivery [38]. Furthermore, the process evaluation will provide rich data relating to the significance of participation to patient participants, and barriers and facilitators to participation in this context.

### Rationale for pain as the primary endpoint

Pain intensity will be measured on Day 3 after TKR surgery using the NRS. Alleviation of pain is a fundamental obligation of healthcare providers, yet clinical studies continue to show that current practices to alleviate pain are unsatisfactory [39, 40]. Poor pain management is associated with serious physiological and psychological sequelae that compromise recovery and negatively affect morbidity and mortality [41]. Suboptimal treatment of acute postoperative pain is also strongly associated with the development of chronic pain [21, 42, 43]. Risk factors for developing chronic post-surgical pain include unrelieved acute pain, persistent severe pain, inappropriate use of analgesics following surgery, as well as patients’ pain-related beliefs [41, 43]. Patient participation in pain treatment decisions can positively influence their postoperative pain experience and lessen risk of progression to chronic pain [40] however studies show that patients have little opportunities to participation in pain management decisions [44].

### Primary endpoint

The primary endpoint for the assessment of patient experience is the “worst pain experienced in the past 24 h” on Day 3 following TKR surgery. Worst pain will be measured using the 0–10 NRS where 0 equates to “No pain” and 10 equates to “Worst possible pain”. Patients will be asked to choose a whole number from 0 to 10 that best describes their worst pain experienced in the previous 24 h.

### Sample size calculation

In this study, the null hypothesis (H_o_) associated with the primary objective is that no difference exists between patients in the intervention group and the control group in terms of worst pain score on Day 3 post TKR surgery. NRS pain intensity scores will be analysed via the fitting of a linear mixed model with random effects for clusters, cohorts within clusters, and, patients within cohorts, and, fixed effects for the conditions. The F-test, conducted at the 5 % significance level, will be used to compare the average pain scores for the two conditions (intervention versus control).

The number of clusters is essentially fixed (i.e. two or possibly three wards) but the number of periods, or cohorts per ward, (2, 3 or 4) and the number of patients in each cohort (24 or 30) was selected in order to achieve 80 % power when there are at least two wards and when the difference (delta) between the average pain scores for the two conditions is 1.65 and at least 70 % power when delta is 1.5. Preliminary (unpublished) data indicate that pain scores decline by 1 to 1.5 units from day 3 to day 4 post TKR surgery and so a delta of 1.5 to 1.65 at 3 days is a similar but enhanced improvement.

Pilot data results also indicated a between-patient (i.e. within-cohort) standard deviation equal to 2 (i.e. between-patient variance component, VP, equals 4) and a grand mean equal to 7. The between-ward variance component (VW) and between-cohorts variance component (VC) were assumed to be equal to 0.025 (this was based on unpublished data for two wards assessed in the same time period).

As the NRS pain intensity score is a bounded discrete outcome score, the power of the F-test was calculated by simulation. Numerical Rating Scale (NRS) observations were generated by adding normal random variables sampled from three distributions (corresponding to the three sources of variation and their specified variance components) to the conjectured fixed effect means and then rounding the result to the nearest whole number in the range of 0–10. In this way, the bounded and discrete nature of the NRS scores was accounted for in analyses of variance (ANOVA) designed for continuous scale variables. For each scenario (combinations of delta, variance components, cohort sizes and ranges of period effects) 10,000 simulations of each “study” were performed and the type II error rate (β) was calculated. The ANOVA directive and programming language in the GenStat statistical system (Release 14.2) were used to perform the simulations [45].

Results of the simulations when period effects are assumed to be equally spaced are shown in Table 4. When the range of the period effects decreases, the power increases. With two wards, the effect difference that would be detectable with 80 % power, when the period effects are in the range from -1 to +1, VW, VC and VP are 0.025, 0.025 and 4 respectively AND when the cohort size is 24, is delta = 1.80, and when the cohort size is 30, delta reduces to 1.65.

**Table 4 Tab4:** Power and sample size calculations (based on two wards and four periods)

Range of period effects	Delta	VW	VC	VP	NP	Power
−1.5, 1.5	1.50	0.025	0.025	4.0	24	0.651
−1.0, 1.0	1.50	0.025	0.025	4.0	24	0.670
−0.75, 0.75	1.50	0.025	0.025	4.0	24	0.680
−1.5, 1.5	1.50	0.025	0.025	4.0	30	0.714
−1.0, 1.0	1.50	0.025	0.025	4.0	30	0.741
−0.75, 0.75	1.50	0.025	0.025	4.0	30	0.744
−1.0, 1.0	1.80	0.025	0.025	4.0	24	0.797
−1.0, 1.0	1.65	0.025	0.025	4.0	30	0.803

Footnote: Power and sample size calculations were calculated for the F test (α = 0.05) for a difference between the intervention and control groups in Day-3 worst pain. Delta is the absolute value of the difference in the mean pain scores. Components of variance in Day-3 pain scores are fixed as follows: between wards (VW = 0.025), between cohorts of patients within the same ward (VC = 0.025) and between patients within a cohort within a ward (VP = 4.0). NP is the number of patients in a cohort. The power (1-β) is the probability that the null hypothesis, of no difference in the mean Day-3 worst pain scores between the control and intervention groups, is rejected when the true, but unknown, difference is delta, the components of variance are as given, there are two wards and four cohorts per ward managed contemporaneously in four time periods, and the F-test is conducted at the 5 % significance level (α = 0.05). In these scenarios, three different ranges (in equally spaced steps) for the effects of the four periods on day-3 worst pain scores are investigated

Four periods and a target of 30 patients per cohort were selected (a total of 240 patients).

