## Data analysis

### Quantitative analysis

Quantitative data obtained through patient questionnaires will be analysed using GenStat statistical system (Release 14.2) and verified using Statistical Package for the Social Science (SPSS V22). Statistical significance will be claimed at *p* <0.05. Descriptive statistics will be used to characterise the study population, and any baseline differences between patients in the control and intervention groups.

The primary endpoint of pain intensity will be compared between groups to determine differences between the intervention and control (usual care). A linear mixed model analysis will be used to calculate the F-test to compare the means of the groups. In a supportive analysis, the REML method will be used to estimate, and if necessary adjust for, period effects. Other outcome measures such as preference for participation, control preference and perceived participation in care will be used to make comparisons between groups and the analyses will use a linear mixed model approach and analogous methods developed for binary and categorical data.

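### The stated primary model omits period, but Table 4's powers match only a model with period fitted; at the protocol's ±1 period effects the stated two-ward model has power of about 0.34 to 0.52, not 0.803

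*Protocol article*

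**What the plan says.** The primary model is set out in the Protocol article under Sample size calculation. It is a "linear mixed model with random effects for clusters, cohorts within clusters, and, patients within cohorts, and, fixed effects for the conditions", and the F-test on condition at the 5% level decides the trial. Period is not among the fixed effects.

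The Quantitative analysis section confirms that this is deliberate, because it deals with period separately: "In a supportive analysis, the REML method will be used to estimate, and if necessary adjust for, period effects".

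The power simulation nevertheless builds period effects into the data. Table 4 uses equally spaced effects over ±0.75, ±1 or ±1.5, and the text notes that "When the range of the period effects decreases, the power increases". The headline result is given for two wards "when the period effects are in the range from -1 to +1": 80% power needs a delta of 1.80 with 24 patients per cohort, and "when the cohort size is 30, delta reduces to 1.65". The sample of 240 rests on that second row (power 0.803). Neither the text nor the table footnote says which terms the simulated ANOVA fitted.

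**The concern.** Leaving real period effects out of the model does not make them disappear. They go into the variation between cohorts within a ward, which is the error term for condition. With eight cohorts, that error term is small when period is removed and large when it is not.

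Table 4 points to a model that removes period. At delta 1.5 with 30 per cohort, stated power moves only from 0.714 to 0.744 as the range shrinks from ±1.5 to ±0.75. If period stayed in the error term, power should change steeply over that range. So the F-test that decides the trial appears not to be the F-test that was powered. What is at stake is a real benefit being declared non-significant.

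**Working it through.** **Inputs**, all from the Protocol article. Sample size calculation and Table 4: grand mean 7; VW = VC = 0.025; VP = 4; cohort sizes 24 and 30; deltas 1.5, 1.65 and 1.8; period effects equally spaced over the stated range; scores rounded to whole numbers and held within 0–10; alpha 0.05. Inpatient data collection section: sequences ABBA and BAAB, giving 2 wards × 4 periods = 8 cohorts.

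**Step 1: reproduce Table 4, then drop period.** Scores were simulated as 7 ± delta/2 + period + ward + cohort + patient, 20,000 runs per row, and condition was tested on the eight cohort means. The models are:
- ward and period fitted: F on 1 and 2 df, critical value 18.51;
- condition only, ward as a stratum: F on 1 and 5 df, critical value 6.61;
- condition only, ward variance pooled to zero: F on 1 and 6 df, critical value 5.99.

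| Period range | Delta | NP | Stated | Period fitted, 2 df | Condition only, 5 df | Condition only, 6 df |
|---|---|---|---|---|---|---|
| ±1.5 | 1.50 | 24 | 0.651 | 0.653 | 0.008 | 0.029 |
| ±1.0 | 1.50 | 24 | 0.670 | 0.675 | 0.222 | 0.353 |
| ±0.75 | 1.50 | 24 | 0.680 | 0.680 | 0.524 | 0.648 |
| ±1.5 | 1.50 | 30 | 0.714 | 0.720 | 0.004 | 0.020 |
| ±1.0 | 1.50 | 30 | 0.741 | 0.736 | 0.224 | 0.374 |
| ±0.75 | 1.50 | 30 | 0.744 | 0.740 | 0.551 | 0.692 |
| ±1.0 | 1.80 | 24 | 0.797 | 0.797 | 0.452 | 0.627 |
| ±1.0 | 1.65 | 30 | 0.803 | 0.802 | 0.340 | 0.520 |

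With ward and period fitted, the largest gap from the stated figure is 0.006, which is simulation error. Other variants do not fit the table. For the last row, period without ward gives 0.92, and REML with ward variance held at zero or above gives 0.52. A patient-level F-test gives about 1.00. A Wald chi-square test gives 0.83 there, but 0.15 against the stated 0.714 at ±1.5, delta 1.5, 30 per cohort. Setting the control mean to 7, rather than centring on 7, leaves the 5-df figure at 0.34.

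**Step 2: why the gap arises (last row, ignoring rounding and bounds).**
- Variance of a cohort mean, given ward and period: VC + VP/30 = 0.025 + 0.133 = 0.158.
- Expected mean square for condition: 8 × (1.65/2)² + 0.158 = 5.445 + 0.158 = 5.603.
- Period fitted: the error mean square is 0.158, so the ratio is 5.603/0.158 ≈ 35, well above 18.51.
- Period omitted: effects −1, −1/3, 1/3 and 1 add a sum of squares of 2 wards × 2.222 = 4.444, spread over 5 df. The error mean square becomes 0.158 + 4.444/5 = 1.047, and the ratio is 5.603/1.047 ≈ 5.4, below 6.61.
- Ward pooled as well: the ward mean square is 0.158 + 4 × 0.025 = 0.258. The error mean square is (5 × 1.047 + 0.258)/6 = 0.916, and the ratio is 5.603/0.916 ≈ 6.1, close to 5.99.

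**Step 3: dependence on the period range (delta 1.65, 30 per cohort).**

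| True period range | Period fitted, 2 df | Condition only, 5 df | Condition only, 6 df |
|---|---|---|---|
| none | 0.81 | 0.99 | 0.99 |
| ±0.5 | 0.81 | 0.91 | 0.95 |
| ±0.75 | 0.81 | 0.69 | 0.81 |
| ±1.0 | 0.80 | 0.34 | 0.52 |
| ±1.5 | 0.78 | 0.01 | 0.05 |

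**Step 4: type I error.** With no treatment effect, the period-fitted test rejects about 5% of the time at every range. The condition-only tests reject about 5% with no period effects, under 1% at ±0.5, and about 0% at ±0.75 and wider.

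**Step 5: bias.** In each period one crossover ward is on intervention and the other on control. With equal cohort sizes the period effects cancel from the treatment contrast, so omitting them inflates the error but does not shift the estimate.

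**The case against.** Four points on the other side deserve weight.

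- **The period effects are assumed.** Table 4 investigates ranges, and no pilot evidence is given for them. If the true range is ±0.5 or less, the model as written is the more powerful one, because it keeps more error degrees of freedom. This stands, and it is why a flat statement that power is 34% would be wrong. It does not remove the mismatch: the smallest range in Table 4 is ±0.75 and the headline range is ±1.
- **No single figure is the model as written.** With two wards and a small VW, a REML fit may set ward variance to zero, giving 0.52 at ±1 and no shortfall at ±0.75 for this delta. This stands too, hence the range.
- **The third ward may enter the analysis.** The article does not say whether it does, and guarantees it no number of patients. Assuming 10 overflow patients per period, condition-only power at ±1 would be 0.51 to 0.85; assuming 30, 0.58 to 0.91 (unweighted cohort means). But Table 4 is explicitly a two-ward calculation, and the comparison here is with Table 4.
- **The article is condensed.** That period was fitted in the simulation is inferred from the figures. The match across eight rows makes the inference strong, but it remains an inference.

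A reader might also infer that the conditional wording on period adjustment lets the trial choose between two p-values after seeing the data. The text does not support this: the condition sits inside the supportive analysis, and the primary F-test is fixed. Nor do the documents support a charge of bias or of inflated type I error; the error runs in the conservative direction.

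**Conclusion.** The concern holds in conditional form. The stated primary model and the model behind Table 4 are different. In the protocol's own headline scenario the stated model has less than half to about two-thirds of the claimed power (0.34/0.803 = 0.42; 0.52/0.803 = 0.65).

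This rests on the protocol's variance components, two wards, equal cohorts of 30 and equally spaced period effects of ±1. At ±0.75 there is a moderate loss or none, depending on how ward variance is handled, and below about ±0.5 there is a gain. The consequence is a possible missed effect through an overstated error term, not a biased estimate or a false positive.

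**What to change.** State the primary model with fixed effects for condition and period (4 levels), together with ward and cohort-within-ward effects, and test condition against the cohort-within-ward residual. Move the period-free model to the supportive analysis. Say in the Table 4 footnote which terms were fitted. If the condition-only model is to stay primary, restate its power over the same period ranges instead.

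The change is one sentence in the analysis text, needs no new data, and should be made before outcomes are compared by group; the article reports that data collection is in its last phase.

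The cost is power if period effects turn out to be small. At ±0.5 or less, the period-fitted test has about 0.81 against 0.91 to 0.99 for the condition-only test. But about 0.80 is what the protocol already claims, and the period-fitted test stays near it across the ranges in Table 4 (0.78 to 0.81 at delta 1.65, 30 per cohort).
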